**Discontinuation of Orthokeratology on Eyeball Elongation (DOEE) Study**

**Proposal by**

**[name]**

**School of Optometry**

**The Hong Kong Polytechnic University**

***Introduction***

Children wearing orthokeratology (ortho-k) have been shown to have slower rate of myopic progression than those wearing single-vision spectacles (Cho et al. 2005) or soft lenses (Walline et al. 2009). Both studies showed that the effect of myopic control was most significant during the first six months of the treatment. It is unknown whether the myopic control effect would dissipate upon the discontinuation of the treatment or whether the myopic control effect only happened in the first six month of lens wear and was maintained thereafter.

Parents of children wearing ortho-k always have questions such as ‘What is the current amount of myopia of the children’, ‘How long do my child need to wear the lenses to slow progression of myopia’ or ‘My child has been on the treatment for a few years. When can s/he stop the treatment?’. In order to answer these questions, to understand the effect of ortho-k more thoroughly, there is a need for a study evaluating the effect of discontinuation of ortho-k treatment on myopic control. This knowledge is necessary and important as patients/parents have concerns about the permanent dependency on ortho-k once they enrolled in the treatment. Would only 6 months ortho-k lens wear (and then switch to spectacles or contact lenses) be adequate for myopic control or does the child need to continue lens wear until s/he is of certain age?

Younger myopic children (aged 6-10 years old) may have the faster increase in myopia than old myopic children (aged 11-15 years old), i.e. the rate of myopic progression may be different in different age groups and in children with different refractive status (Edwards 1999; Fan et al. 2004; Cheng et al. 2007). Although the refractive correction with ortho-k has been well documented, it is unknown whether the efficiency and reversibility of ortho-k for myopic reduction as well as myopic control are similar in children of different age and refractive groups.

***Objectives***

* The primary objectives of this study will be to compare

- eyeball elongation in existing ortho-k subjects who stopped lens wear with subjects who continued ortho-k lens wear and control subjects wearing glasses (Experiment 1)
- rates of change in axial length in younger and older myopic children when corrected with ortho-k and when ortho-k was discontinued (Experiment 2)
- rates of change in axial length in children with faster and slower myopic progression rates (Experiment 2)
- change in corneal parameters during and after discontinuation of lens wear (Experiment 3)

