**Experiment 2.** *Discontinuation of lens wear in new ortho-k children*

The objective of this experiment is to compare axial elongation in younger and older children during ortho-k treatment and after discontinuation of ortho-k lens wear. Forty-five children (aged 6-10) and 45 older children (aged 11-15) who are myopic of 1.50 to 4.50D and who intend to have overnight ortho-k for myopic control will be recruited via advertisement in newspaper or by referral. They should have no previous experience in rigid lens wear and no prior experience in myopic control treatment. The inclusion criteria are listed in Table 3.

Similar to Experiment 1, the subjects will have to participate in a two-phase experiment (see Figure 1).

At the commencement of Phase I (Visit I-0), the subjects’ baseline data will be collected and prescriptions for new spectacles will be determined. New spectacles will be dispensed at Visit I-1. They will be required to use the spectacles in the daytime for the following 6 months (the rest of Phase I). Ortho-k lenses (Menicon Z Night or Menicon Z Night Toric) will be ordered 1 month before the end of Phase I (i.e. Visit I-6), after they have learnt lens handling. Ortho-k lenses, contact lens solutions and daily log will be dispensed at the end of Phase I (Visit I-7) before commencing Phase II (see Table 1). They are required to wear the ortho-k lenses every night in Phase II unless otherwise instructed by their examiner.

Visits schedule and methodology will be the same Experiment 1 (Figure 1 & Table 1).

The study period for each subject will be about 14 months (including 1 month for baseline data collection).

**Experiment 3.** Refractive and corneal changes, including corneal thickness, corneal hysteresis, and corneal resistant factor during ortho-k treatment and the discontinuation of the treatment will be determined. These will be compared in new and existing ortho-k subjects and children of different ages. Information will be collected from subjects participating Experiments 1 and 2.

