***Subjects***

Children between 6-15 years old will be recruited. Informed consent will be obtained from both the parents and the children at the beginning of the study.

- For Experiment 1, 80 ortho-k and 40 control subjects who have completed the 2-year myopic control studies (ROMIO, TO-SEE & HM-PRO) will be recruited. They were 6-12 years old when they joined the myopic control study and will be 8-14 years old when they commence this part of the study. Ortho-k subjects will be randomized into Group OKc where subjects will continue lens wear for another 12 months and Group OKd where subjects will be required to cease lens wear for 6 (+1*) months and wear single-vision spectacles and then resume ortho-k lens wear for another 6 (+1*) months.
- In Experiment 2, two groups of 45 children of aged 6-11 and 12-15 years old, myopia of at least 1.50D and astigmatism of at most 2.50D, and who intend to have overnight ortho-k for myopic control and have no contra-indication for ortho-k lens wear will be recruited via advertisement in newspaper or by referral. Subjects will be monitored for 6 months before they are fitted with ortho-k lenses which they have to wear for 6 (+1*) months.

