**Table 3. Inclusion criteria for new orthokeratology lens wear**

| Age | - 6-15 years of age on the date of recruitment |
| --- | --- |
| Refractive error Myopia  Cylinder | - Non-cycloplegic manifest refraction -  1.50DS and ≤ 4.50DS in manifest refraction - ≤ 3.00DC for axis 18030 or ≤ 1.00DC for other axes |
| Visual acuity | - Best corrected monocular logMAR visual acuity 0.10 or better |
| Ocular health | - Eyes straight at distance and near with best subjective correction - No abnormal ocular health - No ocular conditions which might affect vision or vision development (for example, cataract and ptosis) - No previous rigid contact lenses (including orthokeratology lenses) experience - No contraindications for overnight orthokeratology lens wear. |
| General health | - No systemic conditions which might affect the vision or vision development |
| Others | - No previous experience in myopic treatment (e.g. refractive surgery or progressive lens wear for myopic control) - Willing to wear orthokeratology lenses in accordance with the instructions from practitioner - Willing to follow up the protocol of the study |

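### Experiment 2 promises axial elongation after ortho-k is stopped in new wearers, but its schedule runs spectacles, then ortho-k, then ends, so the objective is wrong as written

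*Protocol*

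**What the plan says.** **Promise.** The Objectives section gives, as a primary objective, "rates of change in axial length in younger and older myopic children when corrected with ortho-k and when ortho-k was discontinued (Experiment 2"). The Experiment 2 section is titled "Discontinuation of lens wear in new ortho-k children" and repeats the aim: to "compare axial elongation in younger and older children during ortho-k treatment and after discontinuation of ortho-k lens wear". Experiment 3 draws on subjects of both experiments for refractive and corneal changes during treatment and its discontinuation, and adds: "These will be compared in new and existing ortho-k subjects and children of different ages".

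**Schedule.** Experiment 2 takes untreated children. Its own section says "They should have no previous experience in rigid lens wear", and Table 3 requires "No previous rigid contact lenses (including orthokeratology lenses) experience". The Subjects section gives the order: "Subjects will be monitored for 6 months before they are fitted with ortho-k lenses", after which the lenses are worn for 6 (+1) months. Figure 1, the Experiment 2 text and Table 1 agree: spectacles in Phase I, lenses dispensed at I-7, nightly wear in Phase II, last visit II-7.

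**The concern.** An effect of discontinuation can be estimated only in children who wore ortho-k, stopped, and were then measured. Experiment 2 has no such period. If the spectacle phase were reported as the discontinuation phase, the paper would draw a conclusion about rebound, or its absence, from measurements taken before any lens was worn.

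The gap touches one of the trial's motivating questions. The Introduction asks whether about six months of ortho-k followed by a switch to spectacles or contact lenses would be enough. Only new wearers who stop early could answer that. The children who do stop, Group OKd in Experiment 1, come from completed 2-year studies.

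**Working it through.** The check is mainly structural: trace what each Experiment 2 child wears and when, and look for an off-lens period after lens wear.

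1. **Exposure at entry.** No rigid or ortho-k lens wear before (Experiment 2 section; Table 3). Time off ortho-k in Phase I is therefore time before treatment.
2. **Phase I, I-0 to I-7.** Spectacles. Table 1 notes that I-1 is the same visit as I-0 for Experiment 2 because there is no refraction-stabilisation (RS) period. This fits: there is no ortho-k effect to wash out.
3. **Phase II, I-7 to II-7.** Nightly ortho-k, with visits II-1, II-3, II-6 and II-7. All four are scheduled during lens wear.
4. **After II-7.** Nothing is scheduled.

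**Does the stated follow-up leave room for an off-lens period?**
- The Experiment 2 section gives about 14 months. Two 7-month phases use 7 + 7 = 14, leaving 14 − 14 = 0.
- The Study period section gives 13 months, although its sum of 6 + 14 + 2 = 22 uses 14. The Subjects section's 6 months of monitoring and 6 (+1) months of lens wear use 6 + 7 = 13, leaving 13 − 13 = 0.

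On either figure, scheduled months off ortho-k after wearing it are 0. The number of children with such a period is 0 of 90 recruited, and so 0 of the 70 intended completers.

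**Text that might point the other way.** The heading on visits during the RS period names all Experiment 2 subjects in Phase II, and the text beneath it describes weekly review after ortho-k has ceased. Set against that:
- The Phase II notes under Figure 1 start the Experiment 2 RS period at I-7, which is when lenses are dispensed.
- Table 1 ends that RS period at II-1, with the rest of Phase II still to come.
- The ortho-k aftercare text ties the weekly visits of the first month of lens wear to the RS period.

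In Experiment 2 the RS period is therefore the settling-in month on lenses. The wording on ceased treatment fits only Group OKd in Phase I.

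**Experiment 3.** Existing wearers (OKd) supply data both off and on lenses. New wearers supply data before and on lenses only. The new-versus-existing comparison can be made for changes during treatment, but not for changes after stopping.

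**The case against.** **Loose wording.** The strongest defence is that the authors meant only off-lens versus on-lens, and that the spectacle phase is the intended comparator. That may be so, and it makes rewording the natural repair. It does not make the present text right: the title and both statements of the objective speak of stopping, and entry is restricted to children with nothing to stop.

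**The rest of the trial stands.** A reader might infer that the study cannot address discontinuation at all, or that Experiment 3 has no data. Neither follows. Group OKd stops and resumes lens wear under observation, and the corneal objective in the Objectives section does not depend on new wearers.

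**Bias in the comparison that remains.** Because every Experiment 2 child has the same order, the within-child change from Phase I to Phase II is confounded with time. A reader might go on to infer a demonstrated bias of known size in favour of ortho-k. The documents do not support that:
- The Introduction says that younger children may progress faster than older ones. It gives no rate of slowing within a child over seven months.
- A time trend common to both age groups cancels from the younger-versus-older contrast. Only a differential trend remains.
- Regression to the mean would matter for "rates of change in axial length in children with faster and slower myopic progression rates (Experiment 2") if fast and slow were defined from Phase I and then compared across phases. The protocol states neither, and the definition may sit in an analysis plan that is not shown. The size is also unsettled. A median split with no treatment effect gives an apparent slowing in the fast half of 0.798 × SD × (1 − correlation). Assuming a 6-month SD of 0.085 to 0.12 mm and a between-phase correlation of 0.3 to 0.7, that runs from 0.798 × 0.085 × 0.3 = 0.020 mm to 0.798 × 0.12 × 0.7 = 0.067 mm. This is a caution and not a finding.

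**Group C as a remedy.** A reader might expect the spectacle controls of Experiment 1 to remove these biases. They cannot be relied on for that. Group C has a separate I-1 visit, will be aged 8-14 rather than 6-15, and may include HM-PRO controls (30 of the 60 potential controls), probably high myopes, whereas the Experiment 2 section limits myopia to 1.50 to 4.50 D.

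**Conclusion.** Wrong as written. A primary objective, the Experiment 2 title and the Experiment 2 objective promise observation after ortho-k is stopped in new wearers, and the schedule provides it for 0 of 90 children. The new-versus-existing comparison of discontinuation changes in Experiment 3 lacks its new-wearer half. This rests on the protocol's own sequence and entry criteria; no assumed SD, correlation or effect size is involved. It is not a matter left to an analysis plan, because analysis cannot create the missing period. Children who withdraw or stop wearing lenses unplanned do not form a scheduled, measured discontinuation phase.

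As designed, Experiment 2 can compare elongation before ortho-k with elongation on ortho-k, by age group, with the within-child change confounded with time.

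**What to change.** Reconcile the objective with the schedule. With the design unchanged:

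1. Restate the Experiment 2 objective as change in axial elongation rate from the pre-treatment spectacle phase to the first ortho-k phase, by age group. Restate the new-wearer part of Experiment 3 in the same way for the refractive and corneal measures.
2. Remove discontinuation from the Experiment 2 title and claims, and limit discontinuation conclusions to Group OKd of Experiment 1.
3. Correct the text on visits during the RS period so that it no longer describes Experiment 2 Phase II as following the end of treatment.
4. State that the within-child Phase II versus Phase I change is confounded with time. It may be shown beside the same change in Group C, adjusted for age and refraction, as a supportive and imperfectly matched comparison.
5. If fast and slow progression are defined from Phase I, warn of regression to the mean when phases are compared.

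**Cost.** Rewording, plus an optional supportive analysis of data already planned. The claims become narrower, and the Introduction's question about six months of ortho-k followed by spectacles is left unanswered.

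The other route is to change the design, which is for the sponsor to decide. For illustration only, an added phase as long as the existing 7-month phases would bring follow-up to 7 + 7 + 7 = 21 months and the Experiment 2 study period to 6 + 21 + 2 = 29 months, against the stated 22 for Experiment 2 and the overall minimum of 28.

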***Study design***

Single masked, prospective study consisting of three experiments.

**Experiment 1**

| **Control** | | | | | | | | | | | | | | | | | | | | | | | | | | | | |
| --- | --- | --- | --- | --- | --- | --- | --- | --- | --- | --- | --- | --- | --- | --- | --- | --- | --- | --- | --- | --- | --- | --- | --- | --- | --- | --- | --- | --- |
| **Continue spectacle-wear** | | | | | | | | | | | | | | | | | | | | | | | | | | | | |
| **Group OKc** | | | | | | | | | | | | | | | | | | | | | | | | | | | | |
| **Continue orthokeratology** | | | | | | | | | | | | | | | | | | | | | | | | | | | | |
| **Group OKd** | | | | | | | | | | | | | | | | | | | | | | | | | | | | |
| **RS** | **SPECTACLES** | | | | | | | | | | | | | **RS** | **ORTHOKERATOLOGY** | | | | | | | | | | | | | |
|  | | | | | | | | | | | | | | | | | | | | | | | | | | | | |
| 1 |  | 2 |  | 3 |  | 4 |  | 5 |  | 6 |  | 7 |  |  |  | 9 | |  | 10 |  | 11 |  | 12 |  | 13 |  | 14 |  |
|  | | | | | | | | | | | | | | | | | | | | | | | | | | | | |
| I-0 | I-1 |  |  |  | I-3 |  |  |  |  |  | I-6 |  | I-7 |  | II-1 | |  |  |  | II-3 |  |  |  |  |  | II-6 |  | II-7 |

**Experiment 2**

|  | **SPECTACLES** | | | | | | | | | | | | | **RS** | **ORTHOKERATOLOGY** | | | | | | | | | | | | |
| --- | --- | --- | --- | --- | --- | --- | --- | --- | --- | --- | --- | --- | --- | --- | --- | --- | --- | --- | --- | --- | --- | --- | --- | --- | --- | --- | --- |
| Month (estimates) |  | | | | | | | | | | | | | | | | | | | | | | | | | | |
| 1 |  | 2 |  | 3 |  | 4 |  | 5 |  | 6 |  | 7 |  | 8 |  | 9 |  | 10 |  | 11 |  | 12 |  | 13 |  | 14 |  |
| Visit |  | | | | | | | | | | | | | | | | | | | | | | | | | | |
| I-0 (baseline) | I-1 |  |  |  | I-3 |  |  |  |  |  | I-6 |  | I-7 |  | II-1 |  |  |  | II-3 |  |  |  |  |  | II-6 |  | II-7 |

Cycloplegic data collection visits Non-cycloplegic data collection visits

I-0 I-3, II-3

I-1, II-1 I-6, II-6

I-7, II-7

**Figure 1. Data collection visits in the experimental phases in the discontinuation study.**

*Data collection visits*

*Phase I*

- Visit I-0 – Commencement of Phase I for all subjects; Commencement of RS period for Group OKd (Experiment 1)
- Visits I-1, I-3, I-6, I-7: about one, three, six and seven months after Visit I-0

*Phase II*

- Visit I-7 – Commencement of Phase II for all subjects; Commencement of RS period for Group OKd (Experiment 1) and all subjects in Experiment 2
- Visits II-1, II-3, II-6, II-7: about one, three, six and seven months after Visit I-7

**Experiment 1.** *Discontinuation of lens wear in existing ortho-k children*

The objective of this study is to compare eyeball elongation in existing ortho-k subjects who stopped lens wear with subjects who continued ortho-k lens wear and control subjects wearing glasses.

Figure 1 shows the required visits for the duration of the experiment for each group of subjects.

In this experiment, subjects who have completed the ROMIO, TO-SEE and HM-PRO studies will be invited to participate. All spectacle-wearing control subjects will be invited to continue as control subjects. Ortho-k subjects will be randomly assigned into Groups OKc or OKd.

All subjects will be followed up for a period of 14 months.

- Group C will continue to wear spectacles for the duration of the experiment
- Group OKc will continue lens wear for the duration of the experiment
- Group OKd will be required to discontinue lens wear for 6 (+1*) months (and wear single-vision spectacles Phase I) and then resume ortho-k lens wear for another 6 (+1*) months (Phase II). *The first month (*) of each phase (See Figure 1), where indicated, is the RS (Refraction Stabilization) period to allow stabilization of refractive errors.*

*Group OKd*

At the beginning of Phase I (Spectacle-wear phase), subjects will be required to wear single-vision spectacles to aid distance vision in the RS period. They are required to use their old spectacles which should be +/– 0.50DS in sphere and +/– 0.50 DC in cylinder from the refraction determined at the time of visit, otherwise, new spectacle lenses will be ordered. They will be followed up weekly until stabilization of refractive errors has been achieved and the stabilized refraction will be used for the prescription of the spectacles which will be delivered at Visit I-1. Once the refraction has stabilized, all children will be required to wear fully-corrected spectacles in the daytime during Phase I. They will be excluded if they regularly use any kind of contact lenses during Phase I.

New ortho-k lenses for these subjects will be ordered one month before the end of Phase I (ie. at Visit I-6) and dispensed at the end of Phase I (Visit I-7) before commencing Phase II (see Table 1).

In Phase II (Ortho-k phase), subjects are required to wear the ortho-k lenses every night unless otherwise instructed by their examiner. They need to attend the ortho-k aftercare visits as scheduled. Complimentary contact lens solutions and lens accessories (Table 2) will be supplied during the treatment. They have to keep an ortho-k journal everyday. Single-vision spectacles may be needed to aid distance vision during the RS period.

Cycloplegic data collection will be conducted at the beginning of each phase, at the end of RS period (for Group OKd only) and at the end of each phase. Subjects will be required to come back for the regular non-cycloplegic data collection visits after RS period. Change in axial length in the 6 months following stabilization of refractive errors for each Phase will be determined and compared within subjects and between groups. The whole study period for each subject will last for about 14 months.

*Group C and Group OKc*

Subjects will wear their habitual spectacles/ortho-k lenses at the commencement of Phase I, before Visit I-1. New glasses will be made based on Rx determined at Visit I-0 and delivery of new glasses will be at Visit I-1 and if indicated (based on data collected at Visit I-6), at Visit I-7 before commencing Phase II. Note that there is no RS period for these two groups of subjects, but cycloplegic and non-cycloplegic data correction visits will be same as Group OKd.

**Experiment 2.** *Discontinuation of lens wear in new ortho-k children*

The objective of this experiment is to compare axial elongation in younger and older children during ortho-k treatment and after discontinuation of ortho-k lens wear. Forty-five children (aged 6-10) and 45 older children (aged 11-15) who are myopic of 1.50 to 4.50D and who intend to have overnight ortho-k for myopic control will be recruited via advertisement in newspaper or by referral. They should have no previous experience in rigid lens wear and no prior experience in myopic control treatment. The inclusion criteria are listed in Table 3.

Similar to Experiment 1, the subjects will have to participate in a two-phase experiment (see Figure 1).

At the commencement of Phase I (Visit I-0), the subjects’ baseline data will be collected and prescriptions for new spectacles will be determined. New spectacles will be dispensed at Visit I-1. They will be required to use the spectacles in the daytime for the following 6 months (the rest of Phase I). Ortho-k lenses (Menicon Z Night or Menicon Z Night Toric) will be ordered 1 month before the end of Phase I (i.e. Visit I-6), after they have learnt lens handling. Ortho-k lenses, contact lens solutions and daily log will be dispensed at the end of Phase I (Visit I-7) before commencing Phase II (see Table 1). They are required to wear the ortho-k lenses every night in Phase II unless otherwise instructed by their examiner.

Visits schedule and methodology will be the same Experiment 1 (Figure 1 & Table 1).

The study period for each subject will be about 14 months (including 1 month for baseline data collection).

**Experiment 3.** Refractive and corneal changes, including corneal thickness, corneal hysteresis, and corneal resistant factor during ortho-k treatment and the discontinuation of the treatment will be determined. These will be compared in new and existing ortho-k subjects and children of different ages. Information will be collected from subjects participating Experiments 1 and 2.

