***Consistency of management***

- Standard fitting protocol will be used to minimize the effect of inter-practitioner difference.
- Both oral and written instructions will be given to the subjects to increase the consistency in lens handling as well as patient compliance.
- Subjects will be asked to keep an ortho-k journal to keep track of lens wear schedule, incidence of lens binding and problems encountered by the subjects. This information will be useful for the assessment of compliance and helpful to the practitioners in giving proper advice in the presence of complication.
- Contact lens solutions will be given and/or purchased (depending on which group) from our clinic and should be replaced at least bimonthly to:
  1. compensate subjects for their time and increase the incentive of the subjects to remain in the study,
  2. encourage regular replacement of contact lens solutions, and
  3. encourage subjects to return for bimonthly visit.

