***Subject number***

From the current ROMIO study, the mean different and SD of the change in axial length in the ortho-k and the control groups who have completed the 12-month lens wear timeline are 0.12 and 0.17mm respectively. To detect a 0.12mm (equivalent to 0.33D) between-group difference for an alpha value of 0.05 and 80% power in 12 months, a sample size of 33 is required for each group.

For Experiment 1, we aim to have at least 66 ortho-k and 33 control subjects completing this study. Allowing for about 15% dropout, we will recruit 80 ortho-k and 40 control children.

*The ROMIO, HM-PRO and TO-SEE studies are ortho-k projects currently being conducted in PolyU. ROMIO and HM-PRO studies are targeting 30 ortho-k and 30 control subjects each and TO-SEE study is targeting for 30 ortho-k subjects. Hence, there will be 90 potential ortho-k and 60 control subjects and so we do not expect difficulties in recruiting the required subjects for this experiment*.

For Experiment 2, we aim to have at least 70 (35 younger and 35 older) subjects completing the study. Allowing for dropouts (including unsuccessful lens wear), we will recruit 90 (45 younger and 45 older) children.

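### The protocol sets two different rules for contact lens wear by Group OKd children in Phase I, both remove randomised children, and nothing accounts for the old lenses or assigns a check on wear between visits

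*Protocol*

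**What the plan says.** All places are in the Protocol.

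- **Experiment 1, Group OKd, Phase I rule.** On children in the stopping phase: "They will be excluded if they regularly use any kind of contact lenses during Phase I". No frequency is attached to regular use.
- **Termination of the study, item 3.** Wearing contact lenses while treatment is discontinued is given as an example of non-compliance for which a child is asked to withdraw. The item has no frequency qualifier.
- **Old lenses.** OKd children come from completed two-year ortho-k studies (Subjects). For Phase II, "New ortho-k lenses for these subjects will be ordered one month before the end of Phase I", and these are dispensed at Visit I-7. No section says what happens to the existing lenses during Phase I.
- **Journal.** "They have to keep an ortho-k journal everyday" stands in the paragraph on Phase II for OKd. Under Experiment 2 the daily log is likewise handed out at I-7 with the lenses. Consistency of management describes a journal of wear schedule, lens binding and problems, names no phase, and says: "This information will be useful for the assessment of compliance".
- **Objective tests.** Table 4a lists refraction, habitual or unaided acuity and Medmont topography, all unmasked, at every data collection visit and every refraction-stabilisation (RS) visit. The text on RS visits uses refraction to decide when stability is reached. No section uses any of these tests to judge whether lenses were worn after I-1.

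**The concern.** OKd versus OKc is the randomised comparison in Experiment 1 and serves the first listed objective. Its outcome is axial elongation over the six months after refraction has stabilised. Two things can distort it in Phase I.

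First, lens nights in OKd that nobody records make OKd resemble OKc. The error runs toward finding that stopping does no harm, and the Introduction says when a child can stop is a question parents ask.

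Second, the rules for handling lens wear act after randomisation and on one arm only. A child in OKc cannot break a ban on lens wear, so this trigger removes children from OKd alone. If those removed differ in elongation from those who stay, the groups are no longer the ones randomisation formed. Because the two sections set different thresholds, the same occasional wearer could be kept by one examiner and withdrawn by another.

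**Working it through.** **Step 1. The two rules side by side**

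| Behaviour of an OKd child in Phase I | Experiment 1, Group OKd | Termination of the study, item 3 |
| --- | --- | --- |
| No lens wear | stays | stays |
| Occasional lens wear | no exclusion stated | asked to withdraw |
| Regular lens wear | excluded | asked to withdraw |

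They disagree in the middle row, which is also the pattern hardest to see.

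**Step 2. What would be seen**

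During the RS period, refraction and corneal shape are reviewed weekly. Stability needs changes of 0.25 D or less between two consecutive visits, with the cycloplegic visit in the following week. After I-1 the data collection visits are I-3, I-6 and I-7. Sustained wear, or wear shortly before a visit, would tend to show on topography, refraction or acuity. Isolated nights well before a visit may not, and no wear record for this phase is named for OKd.

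**Step 3. The planned size, reproduced**

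Inputs from Subject number: the mean difference and SD among children "who have completed the 12-month lens wear timeline are 0.12 and 0.17mm respectively", and for that "between-group difference for an alpha value of 0.05 and 80% power in 12 months, a sample size of 33 is required for each group". A two-sided test is assumed.

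- Normal approximation: n = 2 × (1.960 + 0.842)² × 0.17² / 0.12² = 31.5, so 32. The two-sample t-test gives 32.5, so 33, as stated.
- Completers: "we aim to have at least 66 ortho-k and 33 control subjects completing this study". With 1:1 allocation (assumed; the ratio is not stated) that is 33 in OKd and 33 in OKc.
- Dropout: "Allowing for about 15% dropout, we will recruit 80 ortho-k and 40 control children". Check: 66/0.85 = 77.6, so 78; 33/0.85 = 38.8, so 39. The targets of 80 and 40 cover this.
- Room for losses in OKd: 80/2 − 66/2 = 40 − 33 = 7 children. Removals for lens wear draw on these 7.

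**Step 4. Dilution**

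Assume the effect is proportional to nights worn. If a share p of OKd children wear lenses unseen on a share q of nights, the fraction of the contrast lost is f = p × q. The documents give neither p nor q.

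Power uses SE = 0.17 × √(2/33) = 0.04185 mm and Φ(0.12 × (1 − f)/SE − 1.96).

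| p (assumed) | q (assumed) | f | 0.12 mm becomes | Power, 33 per group |
| --- | --- | --- | --- | --- |
| 0 | 0 | 0 | 0.1200 | 81.8% |
| 20% | 5% | 1% | 0.1188 | 81.0% |
| 20% | 25% | 5% | 0.1140 | 77.8% |
| 20% | 50% | 10% | 0.1080 | 73.3% |

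The second row fits the gap identified in step 2. The last row is wear on half of all nights. On any ordinary reading that is regular use, which both rules already address and the visit tests would probably show. It marks an outer case, not an expectation.

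The power column uses the plan's own 12-month ortho-k versus control figure. The OKd versus OKc contrast covers six months. Whether 0.12 mm suits that window is a separate question; f does not depend on it.

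**The case against.** The strongest case against runs as follows. The Termination section already covers any contact lens wear while treatment is stopped, so occasional wear is not tolerated by the protocol as a whole. Detection does not rest on the family's word: an unmasked examiner sees the child at every visit, with topography and refraction in hand, and the research staff must be experienced ortho-k practitioners (Manpower). Families who refused possible assignment to OKd could join OKc at their own cost, so those randomised had accepted that they might have to stop. The Phase II start of the journal is inferred from where a sentence stands. Custody of lenses is an operational detail, and a sensitivity analysis may be in an analysis plan that is not shown.

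Much of this stands. A reader might infer that only regular use leads to removal, that lens wear in Phase I would go unseen, or that the contrast is likely to shrink by 10% or more. The documents support none of these. The Termination section contradicts the first, the tests in Table 4a weaken the second, and the third needs wear so frequent that it would count as regular.

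Three things remain. The Termination rule conflicts with the Group OKd text rather than settling it. A rule cannot be applied consistently to wear that no one is assigned to look for or record. And withdrawal after randomisation is written into the protocol itself, so an analysis plan cannot recover axial lengths that were never measured.

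**Conclusion.** The point holds as a contradiction between two sections, together with a modest gap in adherence monitoring. The contradiction, the absence of any lens accounting and the lack of an assigned Phase I check can be read directly from the text. That the journal begins in Phase II is an inference: the placement of the OKd sentence and the Experiment 2 dispensing step support it, but the general journal text names no phase.

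The bias from unseen wear has a known direction, toward no difference between OKd and OKc, but no size that the documents can supply. About 1% of the contrast is lost under the assumed 20% of children and 5% of nights, with an effect proportional to nights worn; more frequent wear costs more. The plan has little power in reserve, 81.8% against a target of 80% on its own inputs. The bias from removing children in one arm only has neither a known size nor a known direction. It can be avoided by design, which is the main reason to act.

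**What to change.** 1. Reconcile the Phase I rule under Group OKd with item 3 of Termination of the study, so that both carry one definition of Phase I non-adherence. Which threshold to adopt is for the investigators.
2. Amend both sections so that OKd children who wore lenses stay in axial-length follow-up and are analysed in their randomised group, with a sensitivity analysis that leaves them out.
3. Where families agree, have the clinic hold the old ortho-k lenses from Visit I-0 through Phase I. They have no further planned use, since new ones are ordered for Phase II.
4. At I-3, I-6 and I-7, have the unmasked examiner compare the Medmont maps already scheduled with the I-1 map, ask about lens nights since the last visit, and record the number.

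The cost is a short amendment, a storage step and one field on the case record. No new test or staff is needed. Masking is unaffected: topography is already unmasked, the masked examiner measures only axial length, and the unmasked examiner does not see axial length, so wear is judged without knowledge of the outcome. Some families may not want to hand over their lenses; the other three steps work without that one.
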